### 2.6 Interventions

#### 2.6.1 TAU

Although there is no *gold standard* treatment for FM, in the Spanish healthcare context, the TAU for FM is mainly pharmacological and is adjusted to the symptomatologic profile of each patient. It is usually also accompanied by guidelines for aerobic physical exercise adapted to the individual’s limitations. Participants assigned to this treatment arm will be offered to participate in the FIBRO-On or FIBRO-Out program (whichever is their choice) at the end of the study.

#### 2.6.2 FIBRO-On

This program is also based in the FIBROWALK program (Serrat et al., 2020) and is virtually identical to the FIBRO-Out program described below. The FIBRO-On program will also be administered as an adjuvant intervention to TAU. All contents of the FIBROWALK (explanations and guidelines for the practice of the components of PNE, physical exercise, CBT and mindfulness) will be explained by means of videos together with slide presentations. The contents in the videos will be taught by the first author (MS) who is both a physiotherapist with more than 17 years of experience and a health psychologist with more than 8 years of experience. Furthermore, MS was the creator of the FIBROWALK program. Although the virtual sessions are 60 min long, a general recommendation is to expend 120 min to perform all the exercises indicated in each specific video. Every week, links to the videos of the corresponding module will be sent by email so that patients can access them whenever possible during the week. To limit problems of access to the videos by patients with little technological experience, a highly-accessible and user-friendly platform will be used (e.g. Youtube). To verify that participants adhered to FIBRO-On program, participants will be asked to complete a brief weekly questionnaire (5–10 items) asking for very basic concepts explained in the videos (e.g., “Please, provide a short example of a catastrophic thought”). Participants who do not answer the weekly questionnaire or those informing of any issue interfering with the adherence to treatment protocol (e.g., not being able to do the homework, watching the videos, answering the questionnaire, *etc.*) will be contacted (*via* SMS and/or telephone calls) by the therapist in charge (MS) and some guidance will be facilitated. If necessary, individuals who were unable to view or answer the questionnaire in a specific week could request an extension of the date. There was no therapeutic interaction with the participants, but participants were invited to contact the therapist by email if they experienced any problems. The FIBRO-On program was created during the COVID-19 lockdown and since then, it has been successfully applied at the Central Sensitivity Syndromes Specialized Unit from the HUVH (Serrat et al., 2021a; Serrat et al., 2022b). See Tables 1, 2 for more details.

**TABLE 1 T1:** Outline of the FIBROWALK program (with FIBRO-Out and FIBRO-On specifications).

Educational and psychological contents in the FIBROWALK program
• Pain Neuroscience Education (PNE)
• Cognitive Behavioral Therapy (CBT)
• Mindfulness training (MT)

**Physical therapeutic exercises in the FIBROWALK program**
• Warm-up: activation and mobility exercises
• Therapeutic exercises: moderate aerobic-cardiovascular and muscle strengthening exercises combined with some balance and coordination exercises performed in a playful manner with cognitive and emotional targets (multitask works) where the level of difficulty and dedication time gradually increases
• Cooling-down: flexibility and relaxation exercises

**Homework**
• Moderate intensity walking is recommended from the first session in a progressive pattern: 1st month - once per week, 2 nd month - twice per week, 3rd month - three times per week
• Exercises based on PNE, CBT and MT contents are also proposed every week (e.g., identifying danger signals, modifying sleep habits, challenging negative automatic thoughts, doing a 10-min body scan meditation)
• Double tasks: combining TE with CBT by fostering different cognitive/affective regulation skills throughout exercise (e.g., identifying external and internal stimuli which may promote positive affect during the exercise, discovering automatic thoughts during the exercise and uncovering patterns between thoughts with negative emotions, pain experience and fatigue; diminishing catastrophic thinking; recognizing the achievements, improving self-efficacy)

**Contents in each session#**
Session 1: PNE (1.2) + CBT (1) + MT (1)
Session 2: PNE (3.4) + CBT (2) + MT (2)
Session 3: PNE (5.6) + CBT (3) + MT (3)
Session 4: PNE (7.8) + CBT (4) + MT (4)
Session 5: PNE (9.10) + CBT (5) + MT (5)
Session 6: PNE (11) + CBT (6) + MT (6)
Session 7: PNE (12) + CBT (7.8) + MT (7.8)
Session 8: PNE (13) + CBT (9) + MT (9)
Session 9: PNE (14) + CBT (10) + MT (10)
Session 10: Family Session (PNE 1–16)
Session 11: PNE (15) + CBT (11) + MT (11)
Session 12: PNE (16) + CBT (12) + MT (12)

**Overall structure of the sessions for the FIBRO-Out and FIBRO-On versions of the FIBROWALK program**
**FIBRO-Out program (face-to-face sessions)**
• Review Phase (15′): Brief review of contents of the previous session
• Educational and psychological contents and Physical therapeutic exercises (1h 40′)
• Homework explanation (5′)

**FIBRO-On program (online videos)**
• Review Phase (2′): Brief review of contents of the previous session
• Educational and psychological contents and Physical therapeutic exercises (55′)
• Homework explanation (3′)
Handouts and specific practices are facilitated in each video session and, although the FIBRO-On videos’ duration is of 60 min each, the recommendation is to expend 120 min to do all the exercises proposed

**Note:** Both versions of the FIBROWALK (i.e., FIBRO-Out and FIBRO-On) are equivalent regarding contents and distribution of them across sessions. **#**The numbers between brackets correspond to specific contents of the program explained on Table 2. PNE , pain neuroscience education; CBT , cognitive behavioral therapy; TE , therapeutic exercise; MT , mindfulness training.

**TABLE 2 T2:** Contents of the FIBROWALK program (i.e., Pain Neuroscience Education, Therapeutic Exercise, Cognitive Behavioral Therapy, and Mindfulness Training).

Pain neuroscience education (PNE)
1. Disassembling beliefs
2. Danger signals: modulation and modification
3. Concept of pain, fatigue, and pain system
4. Concept of central nervous system and central sensitization. The role of the brain
5. Acute vs. chronic pain: The purpose of acute pain and how it originates in the nervous central system
6. Pain vs. damage
7. Pain neuromatrix theory and representation of the virtual body
8. Nociception, nociceptors, action potential, peripheral sensitization, and synapses
9. Ascending and descending inhibitory pathways, spinal cord
10. Relationship with attention, perception, pain cognitions, and pain behaviors
11. Allodynia and hyperalgesia, hypersensitivity of the nervous central system
12. Pain memory, pain perception, and autoimmune evaluation error
13. Relationship with stress. Etiology
14. Neuroplasticity and how the pain becomes chronic
15. Relationship with emotions
16. Re-education, gradual activity, and therapeutic exercise
**Therapeutic Exercise (TE)**
1. Essential and necessary movement
2. Set a basal minimum of activity
3. Individualized gradual program
4. Small increases, patterns
5. Activities contingent on the task, not over time
6. Involvement in the tasks of daily life
7. Lifestyle change: cognitive coping strategies
8. Double tasks: focused on the following cognitive/affective targets: positive affect, negative affect, self-efficacy, catastrophic thinking, pain and fatigue
**Cognitive Behavioral Therapy (CBT)**
1. Relaxation and breathing
2. Modulating factors of pain
3. Catastrophizing and fear of movement (fear avoidance model)
4. Painful experiences: confrontation (fear avoidance model)
5. Vital values and setting goals
6. Organization of time
7. Sleep patterns
8. Sexual issues
9. Handling of attention
10. Cognitive restructuring
11. Emotional regulation tasks focused on identifying and promoting a more adaptive use of the following cognitive/affective regulation skills: self-blame, acceptance, rumination, focus on the positive, focus on plans, positive reassessment, put in perspective, catastrophizing, blaming others
12. Troubleshooting
**Mindfulness Training (MT)**
1. An Introduction to Body Scanning
2. Elementary Awareness
3. Sitting Practice and introduction to Yoga
4. Mindfulness and the brain
5. Mindfulness and communication: guilt, empathy, and conflict management
6. Responding vs. reacting
7. Dig deeper into personal practice
8. Mindfulness and Compassion: Strength vs. Cooperation
9. Stress Management
10. Thoughts Management
11. Management of difficult emotions or feelings
12. Dig deeper into personal practice

**Note:** More details on the interventions and program-associated materials and clinical guidelines (Serrat et al., 2022b) can be accessed through a reasonable request to the corresponding author.

#### 2.6.3 FIBRO-Out

The FIBRO-Out program includes the implementation of the 12-session FIBROWALK multicomponent program (Serrat et al., 2020) in an outdoor environment as an add-on to TAU. It will be conducted weekly and in group format (18–20 participants/group) and it will be carried out in a green area in an urban environment (i.e., “Parc del Cargol”) located in the neighborhood of the HUVH (Barcelona). FIBROWALK includes components of PNE, CBT, mindfulness training and therapeutic exercise. PNE aims to reconceptualize pain and is included in all sessions of the program. This is an educational program that teaches pain patients the difference between harm and pain, how the pain program is activated when actual or potential harm is appraised by the brain that seeks to generate an active protective response and how this assessment can be erroneous depending on different contextual factors. It is based on the “Explaining Pain” program by Butler and Moseley (2010). Examples, images and metaphors are used to facilitate the understanding of the educational content of the program (Nijs et al., 2011). Multi-component physical exercises such as stretching, balance training, posture correction, limb extension and low-impact walking (i.e., Nordic walking) are performed with a moderate training load. Exercises are individualized, establishing a baseline of minimum performance and guiding progression throughout the 12-week program. Following the recommendations of the *American College of Sports Medicine* (Pescatello et al., 2014), each therapeutic physical exercise session is structured in three parts: warm-up, main exercise and cool-down. At the beginning of each session, an interval of approximately 15 min is set aside to discuss the most important aspects of the task between sessions, as well as to review the concepts already explained in the previous treatment sessions. The psychological approach in the FIBROWALK program is based on CBT and aims to promote cognitive changes (e.g., reduce catastrophizing about pain), improve emotional regulation, increase sleep quality, enhance problem-solving strategies and facilitate the establishment of life values and goals (Moix and Kovacs, 2009). Mindfulness exercises are also performed with the aim of training attention to present experience and fostering a non-evaluative attitude towards that experience (Kabat-Zinn, 2013). Mindfulness exercises are based on the Mindfulness-Based Stress Reduction (MBSR) program (Kabat-Zinn, 2013), for which evidence of efficacy and cost-effectiveness in FM patients has been demonstrated (Pérez-Aranda et al., 2019). CBT and mindfulness training help patients to become aware of their own thoughts, emotions and behaviors so that, once identified, they can be regulated or managed facilitating the same situation (e.g., pain) to be experienced in a more flexible and fulfilling way, with less associated suffering. Consistent with PNE, directing attention to the present (rather than to future concerns or past losses or threats) may provide the appropriate safety setting to reduce the perception of alarm or danger associated with pain and allow for successful re-education of the pain program (Moseley G. L., 2003; Moseley L., 2003; Moseley et al., 2015). The framework of motivational interviewing (Nijs et al., 2020) and the cognitive-behavioral model of fear avoidance (Vlaeyen et al., 1995) are part of the theoretical background of CBT in the FIBROWALK program. The intervention is carried out by encouraging social interactions, supported by *role-playing* techniques to promote understanding of content and enhance adherence to treatment. In order to promote an adequate motivational state for the performance of all the exercises and practices in the FIBROWALK program, individualized modifications will be proposed following the trans-theoretical model of stages of change (Prochaska, 2008). For a summary of the contents of the FIBROWALK program, see Tables 1, 2.

In RCTs of non-pharmacological treatments, it is recommended that more than one therapist deliver each treatment to create a more realistic and generalizable impression of effectiveness (Ost, 2014). FIBRO-Out intervention will be conducted by six different therapists (i.e., three health psychologists and three physiotherapists) with experience in the field of chronic pain and FM. Psychotherapists and physiotherapists will work in pairs in each study group, leading psychotherapeutic or physiotherapeutic FIBROWALK components. The physiotherapist in charge of the group will conduct the first block of each session of the program (PNE + therapeutic exercise; 1 h duration) and the psychologist will conduct the second block (CBT + mindfulness; 1 h duration). Four different pairs of therapists will be generated to lead the four FIBRO-Out groups (18–20 participants per group) that will be carried out for this study. The outdoor FIBROWALK program has already been the subject of a previous investigation by the group (Serrat et al., 2020) and very high levels of adherence were observed, with 90% of patients attending 10 or more sessions out of 12.

### 2.7 Treatment fidelity evaluation of the FIBRO-Out arm

All therapists involved in this treatment arm will have prior experience in CBT or physiotherapy applied to individuals with FM or chronic pain and will receive an 8-h face-to-face training prior to starting the RCT with the aim of standardization. The six therapists in the FIBRO-Out program will be trained by fulfilling the FIBRO-On program (which includes all the same components as the outdoor format) and participating as co-therapists in a brief FIBRO-Out program (i.e., 4 sessions, 2 h each) for people with FM with the close face-to-face supervision of the clinical manager of the study (MS). All program-related doubts raised in each training session will be shared within the therapist group and solved by MS. Furthermore, every week during the intervention, meetings will be held between the therapists and MS to allow them to discuss any difficulties experienced and find ways to overcome them. To allow quality control of the provided treatment, the training of the therapists will be based on the FIBROWALK manual and guidelines (Serrat et al., 2021a; Serrat et al., 2021b; Serrat, 2022a) and the therapists will be evaluated for treatment fidelity for independent experts at the end of their intervention. This program manual will be used for training, supervision of the therapists and also for monitoring the program’s quality and performance. To monitor treatment fidelity within the FIBRO-Out arm, research assistants will audio-tape all treatment sessions and two independent experts in the program will rate adherence to each component of the FIBRO-Out. A random sample of tapes, stratified by therapist and therapy session will be rated using the instruments described below. Treatment fidelity will be assessed with a measure of fidelity criteria based on the guidelines for the FIBROWALK intervention, which will be generated by MS before the start of the interventions. The results of the evaluation of the therapist’s adherence to the program will not only allow monitoring of the program’s quality but also allow providing detailed feedback to the therapists about their performance.

All study participants will be asked to continue taking the same medication regimen for the duration of the study period (6 months).

### 2.8 Study measures

Assessment of outcome and process measures will be carried out at baseline, 6 weeks after starting treatment, at post-intervention (12 weeks) and at 6-month follow-up after starting the trial (follow-up. Cost-utility assessment will be conducted at baseline and at the follow-up and biomarkers evaluation at baseline and post-intervention. The research assistants in charge of the evaluations will be extensively trained by researchers (MS, [name]), who have broad experience in applying the study measures.

The following domains will be assessed (see Table 3 for a summary of assessments):- Socio-demographic questionnaire: gender, date of birth, marital status, cohabitation, educational level and employment status.- Clinical data: date of FM diagnosis, years with a FM diagnosis, comorbidity with other diagnosed medical/psychiatric conditions, type and dosage of current medication, weight and height.

**TABLE 3 T3:** Summary of the assessments in the RCT.

	Baseline	6 weeks	Post-intervention (12 weeks)	Follow-up (6 months)
Sociodemographic and clinical characteristics of the sample				
Sociodemographic data	X			
Clinical data	**X**			
Primary outcome measure				
FIQR	**X**	**X**	**X**	**X**
Secondary outcome measures				
VAS Pain	**X**	**X**	**X**	**X**
VAS Fatigue	**X**	**X**	**X**	**X**
HADS	**X**	**X**	**X**	**X**
PSS	**X**	**X**	**X**	**X**
PF-SF-36	**X**	**X**	**X**	**X**
B-PSQI	**X**	**X**	**X**	**X**
MISCI	**X**	**X**	**X**	**X**
CSI	**X**	**X**	**X**	**X**
PGIC/PSIC			**X**	
Process measures				
PCS	**X**	**X**	**X**	**X**
TSK-11	**X**	**X**	**X**	**X**
PIPS	**X**	**X**	**X**	**X**
R–NPQ	**X**	**X**	**X**	**X**
Cost-utility measures				
CSRI	**X**			**X**
EQ-5D	**X**			**X**
Other self-reported measures				
CEQ	**X**		**X**	
Perceived adverse effects of the interventions		**X**	**X**	
Fidelity evaluation (adherence of the therapists to the FIBROWALK guidelines)			**X**	
physiological markers				
Immune-inflammatory markers	**X**		**X**	
BDNF	**X**		**X**	

Note: BDNF, Brain-Derived Neutrophic Factor; B-PSQI, brief version of the pittsburgh sleep quality index; CEQ, Credibility/Expectancy Questionnaire; CSI, central sensitization inventory, short form; CSRI, client service receipt inventory; HADS, hamilton anxiety depression scale; MISCI, multidimensional inventory of subjective cognitive impairment; PCS, Pain Catastrophizing Scale; PF-SF-36, Physical Function from the Short Form-36 Health Survey; PGIC/PSIC, Patient Global Impression of Change/Pain Specific Impression of Change; PIPS , psychological inflexibility in pain scale; PSS, perceived stress scale; R-NPQ, revised neurophysiology of pain questionnaire; TSK, tampa scale for kinesiophobia; VAS, Visual-analogue scale.

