## Abstract

**Introduction:** The On&Out study is aimed at assessing the effectiveness, cost-utility and physiological underpinnings of the FIBROWALK multicomponent intervention conducted in two different settings: online (FIBRO-On) or outdoors (FIBRO-Out). Both interventions have proved to be efficacious in the short-term but there is no study assessing their comparative effectiveness nor their long-term effects. For the first time, this study will also evaluate the cost-utility (6-month time-horizon) and the effects on immune-inflammatory biomarkers and Brain-Derived Neurotrophic Factor (BDNF) levels of both interventions. The objectives of this 6-month, randomized, controlled trial (RCT) are 1) to examine the effectiveness and cost-utility of adding FIBRO-On or FIBRO-Out to Treatment-As-Usual (TAU) for individuals with fibromyalgia (FM); 2) to identify pre–post differences in blood biomarker levels in the three study arms and 3) to analyze the role of process variables as mediators of 6-month follow-up clinical outcomes.

**Methods and analysis:** Participants will be 225 individuals with FM recruited at Vall d’Hebron University Hospital (Barcelona, Spain), randomly allocated to one of the three study arms: TAU vs. TAU + FIBRO-On vs. TAU + FIBRO-Out. A comprehensive assessment to collect functional impairment, pain, fatigue, depressive and anxiety symptoms, perceived stress, central sensitization, physical function, sleep quality, perceived cognitive dysfunction, kinesiophobia, pain catastrophizing, psychological inflexibility in pain and pain knowledge will be conducted pre-intervention, at 6 weeks, post-intervention (12 weeks), and at 6-month follow-up. Changes in immune-inflammatory biomarkers [i.e., IL-6, CXCL8, IL-17A, IL-4, IL-10, and high-sensitivity C-reactive protein (hs-CRP)] and Brain-Derived Neurotrophic Factor will be evaluated in 40 participants in each treatment arm (total n = 120) at pre- and post-treatment. Quality of life and direct and indirect costs will be evaluated at baseline and at 6-month follow-up. Linear mixed-effects regression models using restricted maximum likelihood, mediational models and a full economic evaluation applying bootstrapping techniques, acceptability curves and sensitivity analyses will be computed.

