#### 2.8.3 Cost-utility measures

- *Client Service Receipt Inventory* (CSRI; Vázquez-Barquero et al., 1997). The CSRI is a questionnaire for economic evaluation. The version used in this study is designed to retrospectively collect data on the use of health and social services during the previous 6 months.

- EuroQoL-5D-5L (EQ-5D-5L; Badia et al., 1999). The EQ-5D-5L is an instrument for assessing health-related quality of life. It consists of two parts: the first part assesses the individual’s difficulties in relation to mobility, self-care, pain/discomfort and anxiety/depression; and the second part assesses the patient’s current perceived health status on an analogue-visual scale from 0 (“the worst health you can imagine”) to 100 (“the best health you can imagine”).

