The utilities represent the rating of the patients’ quality of life on a scale from 0 (“as bad as death”) to 1 (“perfect health”). For the cost-utility analysis, the ratio between the cost of each intervention and its consequences in terms of QALYs will be calculated. QALYs will be computed using Spanish EQ-5D tariffs. Following the International Society for Pharmacoeconomics and Outcomes Research (ISPOR) core recommendations for cost-effectiveness analyses alongside RCTs (Ramsey et al., 2015), we will calculate the incremental cost-utility ratios (ICUR) for each pairwise comparison (TAU vs. FIBRO-On, TAU vs. FIBRO-Out, FIBRO-On vs. FIBRO-Out), defined as the difference in mean costs divided by the difference in mean QALYs. Given that the duration of the study is 6 months, neither costs nor outcomes are subject to discounting. QALYs at 6 months after the start of the interventions will be approximated by calculating the area under the curve.

Cost-effectiveness analyses will be performed using the Zellner’s seemingly unrelated regression (SUR) model (Greene, 2003) with the STATA’s *sureg* command. Using the SUR method for cost-effectiveness purposes implies the use of a bivariate system of regressions that includes both costs and outcomes (with the latter being either QALYs or EurQol-5D-5L VAS, depending on the model considered) as the dependent variables of the two separate equations, which will be estimated jointly. The regressions of costs and outcomes are therefore part of two regressions on treatment allocation (i.e., whether they are assigned to TAU, FIBRO-Out, or FIBRO-On) plus an additional set of control variables (measured at baseline) if necessary: age, gender, marital status, education level, employment status, baseline costs, or baseline outcome, depending on the equation considered.

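### With EQ-5D-5L taken only at baseline and 6 months, the QALY gives any utility difference at 12 weeks zero weight, and adjustment for baseline utility and cost is left optional

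*Protocol article*

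**What the plan says.** On timing, Section 2.8 reads "Cost-utility assessment will be conducted at baseline and at the follow-up". Table 3 agrees, marking the EQ-5D and the CSRI only at those two times, and so does the Abstract: "Quality of life and direct and indirect costs will be evaluated at baseline and at 6-month follow-up". The FIQR, most secondary outcomes and all process measures are also taken at 6 weeks and "at post-intervention (12 weeks) and at 6-month follow-up after starting the trial".

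On the QALY, Section 2.11.3 says "QALYs at 6 months after the start of the interventions will be approximated by calculating the area under the curve". The visual-analogue part of the EQ-5D-5L is described in Section 2.8.3 as rating "current perceived health status on an analogue-visual scale".

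On costs, the CSRI is "designed to retrospectively collect data on the use of health and social services during the previous 6 months" (Section 2.8.3). Section 2.11.3 adds the cost of the staff who run the interventions.

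On the model, Section 2.11.3 regresses costs and outcomes jointly on allocation, "plus an additional set of control variables (measured at baseline) if necessary". The list of possible controls ends with "baseline costs, or baseline outcome, depending on the equation considered". No criterion for necessity is given.

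**The concern.** Both programmes last 12 weeks. The existing evidence is short-term, and whether effects last to 6 months is a question the trial sets out to answer (Section 3). The two-point QALY rests entirely on the later time. Whatever utility the arms gain by the end of treatment is not measured, and a questionnaire that rates current health cannot recover it at 6 months. The cost side does cover the whole period, so the incremental ratio sets complete costs against a partly unobserved effect.

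The covariate wording adds a second weakness with the same root. When the QALY is built from two values, one of them is baseline utility, so any chance difference between arms at baseline enters the incremental QALY arithmetically. If the analyst may decide whether to adjust, two defensible estimates exist and the choice can be made after seeing them.

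Cost-utility is part of objective 1, and the Discussion ties a recommendation for standard care to cost-effectiveness, so the result has consequences. The primary FIQR analysis is not affected.

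**Working it through.** The article states no utility, QALY or cost-per-QALY figure, so there is none of its own to reproduce. Inputs from the article: measurements at 0 and 6 months (taken as 26 weeks), an existing assessment at 12 weeks, and 75 participants per arm. Utility gains, utility SD and correlation are assumptions.

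**1. Weights.** Let D12 and D26 be the between-arm utility differences at 12 and 26 weeks, with no difference at baseline.

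- Two points: 0.5 × (0 + D26)/2 = 0.25 × D26.
- Three points: (12/52) × D12/2 + (14/52) × (D12 + D26)/2 = (26/104) × D12 + (14/104) × D26 = 0.25 × D12 + 0.1346 × D26.

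**2. Break-even.** The two agree when 0.25 × D12 = (0.25 − 0.1346) × D26, so D12 = 0.46 × D26. This is the straight line itself, since 12/26 = 0.46. Each 0.01 of 12-week difference above or below that line is worth 0.25 × 0.01 = 0.0025 QALY.

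**3. Scenarios (assumed gains).**

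| Course of effect | D12 | D26 | Two-point | Three-point | Two-point error |
|---|---|---|---|---|---|
| Maintained | 0.05 | 0.05 | 0.0125 | 0.0192 | 35% too low |
| Half faded | 0.05 | 0.025 | 0.0063 | 0.0159 | 61% too low |
| Fully faded | 0.05 | 0 | 0 | 0.0125 | all missed |
| Late | 0.01 | 0.05 | 0.0125 | 0.0092 | 35% too high |

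The percentages depend only on the ratio D12/D26, so doubling every gain leaves them unchanged. With a positive incremental cost, the cost per QALY would be 1.54 times as high (0.01923/0.0125) in the maintained case and 2.54 times as high (0.01587/0.00625) in the half-faded case.

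**4. Chance baseline imbalance.** Assume utility SD 0.20 and a baseline to 6-month correlation ρ of 0.4 to 0.6.

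- Standard error of the baseline difference: 0.20 × √(2/75) = 0.033.
- An imbalance of that size shifts the unadjusted QALY difference by 0.25 × (1 + ρ) × 0.033, which is 0.011 to 0.013. That is about as large as a true gain of 0.0125.
- For SD 0.15 to 0.25 the same shift runs from 0.009 to 0.016.

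**5. Precision.**

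- Unadjusted SE: 0.25 × 0.20 × √(2(1 + ρ)) × √(2/75) = 0.0137 (ρ = 0.4) to 0.0146 (ρ = 0.6).
- Adjusted SE: 0.25 × 0.20 × √(1 − ρ²) × √(2/75) = 0.0075 to 0.0065.
- The ratio is √(2/(1 − ρ)) = 1.83 to 2.24, whatever the SD or sample size.

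A simulation of 10,000 trials per correlation agrees: unadjusted SD 0.0137 to 0.0145, adjusted 0.0075 to 0.0065. The unadjusted mean was 0.0125 to 0.0126 for a true 0.0125, so there is no bias on average. In trials with a baseline imbalance near 0.03, the unadjusted estimate averaged 0.023 to 0.024 and the adjusted one 0.012.

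**The case against.** **Direction.** A reader might infer that the schedule misses a 12-week peak, so that QALY gains are systematically understated. The article does not say that the effect peaks at 12 weeks; it says only that maintenance is unknown. A late-developing effect reverses the sign. For FIBRO-On against FIBRO-Out the direction depends on two unknown trajectories. All of this stands. Understatement does not need a peak, however: a merely maintained effect is enough.

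**Ratio multipliers.** They need a positive incremental cost. The article gives no cost difference, and savings in service use or medication are possible. The three-point area is also an approximation. Both remarks stand.

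**Bias.** A reader might conclude that optional adjustment biases the cost-utility result. Under randomisation it does not; the simulation shows this. The harm is lost precision, distortion when an imbalance occurs, and discretion.

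**Level of document.** A final covariate set is commonly left to the analysis plan, and the article already pairs baseline outcome and baseline cost with their equations. That limits the criticism. What remains is that the article states the adjustment as conditional.

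**Costs.** Baseline cost is not part of the trial-period cost in the way baseline utility is part of the QALY. It matters only through correlation, so the case for adjusting the cost equation is precision and pre-specification.

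**Burden.** Section 2.5 describes the baseline battery as online. That the later assessments are online too is an inference.

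The complete-case and per-protocol scenarios in Section 2.11.3 address neither part.

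**Conclusion.** The point holds in a limited form. Two-point QALYs ignore utility at the end of treatment. Against TAU they would understate the gain by about 35% if a 12-week effect is maintained and by about 61% if it half fades. They would overstate it if the 12-week difference is below about 46% of the 6-month difference. For the comparison of the two active arms the direction is unknown. These sizes rest on assumed utility courses; the weights of 0.25 and 0.1346 follow from the schedule alone.

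Leaving out baseline utility roughly doubles the standard error of the incremental QALY for correlations of 0.4 to 0.6. It also leaves the estimate exposed to chance imbalance and the model open to later choice. It does not bias the estimate on average. Both weaknesses are worth correcting because cost-utility belongs to objective 1; neither touches the primary endpoint.

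**What to change.** 1. In Table 3 and Section 2.8, add the EQ-5D-5L to the existing 12-week assessment, and preferably also to the 6-week one, in all three arms. In Section 2.11.3, compute QALYs from all measured points. Cost: a small amendment and a minute or two per participant.
2. If the schedule can no longer change, state in Section 2.11.3 that utility is assumed to move in a straight line from baseline to 6 months. Test this in a sensitivity analysis that sets the 12-week difference both above and below that line, at 0.0025 QALY per 0.01 of utility. Cost: analysis time only.
3. In every scenario of the seemingly unrelated regression model (imputed, complete-case and per-protocol), always include baseline utility in the QALY equation and baseline cost in the cost equation. Remove the conditional wording for these two; the other controls can stay optional under a rule set in advance. Both variables are already collected, so this costs nothing and can be done even if assessments have begun. It remains worthwhile with a 12-week measurement, because baseline utility then still carries a weight of 12/104 = 0.115.
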